#### 6.4.1 Compliance and Adherence

The study PIPs will be working closely with the care home staff and the resident's GP, and will be reporting regularly to both parties. The local researcher will also maintain regular contact with the PIP to ensure that study procedures are being properly carried out, according to the study training package. During the study there will be a check of a random 20% sample of the pharmaceutical care plans and associated resident documents by a study geriatrician, to ensure clinical appropriateness and safety. Should any problem arise, the geriatrician will discuss this with the CI and PI. See Section 6.11.2.1 for details.

### 6.5 Outcomes

Outcome data on residents will be collected at baseline, three months (falls and EQ-5D only) and at the end of the intervention period of six months, using standard, validated approaches:

#### Primary Outcome

- fall rate per person at 6 months; as documented in care home falls record

## Secondary Outcomes

- proxy EQ-5D-5L (quality of life) at baseline, 3 months and 6 months
- face to face self-reported EQ-5D-5L (only applicable for participants with capacity) at baseline, 3 months and 6 months
- proxy Barthel Index (physical functioning) at baseline and 6 months
- fall rate per person in past three months at baseline and 3 months
- health-service utilisation (and associated costs) in past three months at baseline and in past 6 months at 6 months follow up
- mortality
- change in hospitalisation rate per person (baseline rate defined as 3 months prior to randomisation compared with hospitalisation rate at 6 month follow up)
- Drug Burden Index (DBI) at baseline and 6 months

In addition, in the internal pilot stage we will monitor the following to confirm the feasibility of the full RCT:

- sufficient interest from medical practices-PIPs-care home(s) to confirm viability of planned target recruitment numbers and time line
- >30% of eligible patients recruited (from those invited in each home)
- >80% of data available at 3 months for falls data
- no significant intervention related safety concerns

### 6.5.1 Further Outcomes

#### 6.5.1.2 Process Outcomes

In addition we will collect the following process outcomes per participating resident:

- Number of medications: This will be derived from the medication records, collected for both intervention and control arms, at each stage, and will be used to describe the participant characteristics as well as the intervention (in the intervention group only)
- Use of antipsychotic drugs (a class of medicines used to treat psychosis and other mental and emotional conditions). This will be derived from the medication records collected for both intervention and control arms, at each stage, and will be used to describe the participant characteristics as well as the intervention (in the intervention group only). In addition, this will be included in calculating the DBI in both groups.
- Duplicate drugs: Information about duplicate drugs (both true drug duplicates and therapeutic drug duplication) will be collected in the intervention group by the PIPs when they record this in the PCP as a reason for a PIP intervention and will be used to describe the intervention

#### 6.5.1.3 Health Economic

Costs to the NHS and cost implications for the care home; for full description, see **Section 6.9.5.1**,

For a full list of all the data that will be collected from participants, please see Appendix 3.

## 6.6 Figure 1. Participant Timeline

|                                                                                                                                                                |                |                                              | STUDY PERIOD                                 |                                              |
|----------------------------------------------------------------------------------------------------------------------------------------------------------------|----------------|----------------------------------------------|----------------------------------------------|----------------------------------------------|
|                                                                                                                                                                | Enrolment      | Start of Intervention
(baseline)          |                                              | End of intervention                          |
| TIMEPOINT                                                                                                                                                      | t 0 | t 1
0 months
(+/- one week) | t 2
3 months
(+/- one week) | t 3
6 months
(+/- one week) |
| ENROLMENT:                                                                                                                                                     |                |                                              |                                              |                                              |
| Eligibility screen                                                                                                                                             | X              |                                              |                                              |                                              |
| Informed consent (including a capacity assessment)                                                                                                             | X              |                                              |                                              |                                              |
| INTERVENTION: All participants in the intervention group will receive the intervention which consists of a PIP working with their GP to manage their medicines |                |                                              |                                              |                                              |
|                                                                                                                                                                |                |                                              |                                              |                                              |
| DATA COLLECTION                                                                                                                                                |                |                                              |                                              |                                              |
| Qualitative interviews with a purposive sample of residents, relatives, care home staff, GPs and PIPs                                                          |                |                                              |                                              | X                                            |
| Proxy Barthel ADL, face to face EQ5D                                                                                                                           |                | X                                            | X                                            | X                                            |
| Proxy EQ-5D-5L                                                                                                                                                 |                | X                                            | X                                            | X                                            |
| Care home adverse drug events                                                                                                                                  |                |                                              | X                                            | X                                            |
| Drug Burden Index                                                                                                                                              |                | X                                            |                                              | X                                            |
| Fall rate per person in past 3 months                                                                                                                          |                | X                                            | X                                            | X                                            |

|                                                                                          |                 |             |             |   |
|------------------------------------------------------------------------------------------|-----------------|-------------|-------------|---|
| Hospitalisations                                                                         |                 | x           |             | x |
| Prospective SAE/near miss data recording and notification by PIP, GP and care home staff | Ongoing from t0 | Ongoing     | ongoing     | x |
| Retrospective SAE/near miss data collection by RA/CTU Trial Manager                      |                 | X (monthly) | X (monthly) | X |

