## **6.4 Interventions**

The intervention will be delivered by trained PIPs for a period of six months. The intervention has already been tested in the earlier feasibility study and will involve the PIP, in collaboration with the care home resident's GP, assuming responsibility for managing the medicines of the resident, which will include:

- reviewing resident's medication and developing and implementing a pharmaceutical care plan
- assuming prescribing responsibilities
- supporting systematic ordering, prescribing and administration processes with each care home, GP practice and supplying pharmacy where needed
- providing training in care home and GP practice
- communicating with GP practice, care home, supplying community pharmacy and study team

Details of the intervention are in the CHIPPS Service Specification (Appendix 2) developed in previous work packages. It includes the actions, which the PIP will undertake, and are described below.

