## 6.7 Randomisation

The study is a 2-arm cluster-randomised controlled trial, which will recruit using recruitment triads. A recruitment triad (i.e. the randomised cluster) consists of 1 GP practice plus 1 PIP plus a mean of 20 residents from at least one care home. Following recruitment of the triad, it will be randomised to either the intervention or control groups. Randomisation will be performed using a web-based electronic randomisation system integrated into the study database.

Figure 2. Study flow chart

[figure not shown]

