## 6.9 Recruitment and Retention

### 6.9.1 Recruitment

We will recruit a total of 44 triads; each triad will consist of 1 GP + 1 PIP + a mean of 20 care home residents, from at least 1 care home. Recruitment will be in sequential phases: Pilot, Phase 1, Phase 2 and Phase 3 (see diagram 3 below). Each of these phases encompasses all elements of the study – identification, recruitment and formation of the triads (GP, PIP and care home/s), recruitment of resident participants, randomisation and PIP training for the intervention group.

It is envisaged that recruitment will be equal across all four locations, but some variation across locations is expected.

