### 6.9.2 Retention of participants

The intervention will be delivered over a period of six months, during which time we do not expect many participants to drop out. However, it is likely that, due to the age and frailty of the population and based on our experience in previous studies, some of our participants may die in the six months intervention period and some may move. In either case, all data will be collected up to the end of the participant's study participation. However, if a participant dies, or withdraws, before the intervention has begun, then they can be replaced.

If a participant is excluded, as a post randomisation exclusion, they may be replaced, if this can be done within two weeks of the beginning of the intervention.

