#### **6.10.4 Statistical Methods**

##### **6.10.4.1 Statistical Analysis Plan**

The primary outcome ('falls per patient') will mostly likely follow a Poisson distribution and a between group comparison to estimate the difference in falls will be made using a Poisson Regression model. This model will include baseline fall rate, prognostic variables (specified prior to analysis) and group as a fixed factor. The unit of analysis will be the individual participant but, due to the study design incorporating 'clustering' these unit outcomes are likely to be correlated. Therefore, a Generalised Estimation Equation (GEE) approach will be used. The Poisson assumption will be assessed with 'fit' statistics and, if appropriate, a Zero Inflated Poisson, or a Poisson model with an over-dispersion term will be considered.

An analogue GEE model will be used for secondary outcomes, with an appropriate change to the error distribution (e.g. Normal).

The estimate of the between group difference will be provided with a 95% confidence interval and tested at the 5% significance level.

A full Statistical Analysis Plan (SAP) will be written prior to the end of data collection and approved by the study DMC.

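### Baseline is timed to the start of the intervention, give or take a week, which falls after randomisation and can run into delivery; it should be completed before allocation is disclosed

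*Protocol*

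**What the plan says.** Protocol section 6.6, Figure 1, heads the t1 column "Start of Intervention (baseline" and gives its timing as "0 months (+/- one week". Baseline proxy and face-to-face EQ-5D, proxy Barthel, Drug Burden Index, falls in the previous three months and hospitalisations all sit in that column.

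On the order of events:
- Section 6.7: "Following recruitment of the triad, it will be randomised to either the intervention or control groups".
- Section 6.9.1 ends its list of the elements of each recruitment phase with "recruitment of resident participants, randomisation and PIP training for the intervention group".
- Section 6.4: "The intervention will be delivered by trained PIPs for a period of six months".

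On the look-back, section 6.5 (Secondary Outcomes) counts baseline falls and health-service use over the three months before baseline, but defines the hospitalisation comparison differently: "baseline rate defined as 3 months prior to randomisation compared with hospitalisation rate at 6 month follow up".

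On use and raters, section 6.10.4.1 says of the primary model: "This model will include baseline fall rate, prognostic variables (specified prior to analysis) and group as a fixed factor". Secondary outcomes get an analogous model. Section 6.10.5.1 has a member of the care home staff complete the proxy EQ-5D-5L. No rater is named for the Barthel.

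**The concern.** A baseline should be untouched by allocation. If it is measured after the home and practice can know their arm, two things can go wrong. A subjective rating can shift with knowledge of the arm. A record-based measure can also pick up early effects of the intervention, and adjusting for it then removes part of the effect being estimated.

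The staff-rated EQ-5D-5L is open to the first problem, because the text shown describes no masking of care home staff. The Drug Burden Index is open to the second, because medication review and deprescribing are what the pharmacist is there to do. Baseline fall rate matters because it enters the primary model explicitly.

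There is also a symmetry problem. Control homes have no intervention to start, so nothing fixes their baseline date, and the two arms could be assessed at different distances from randomisation.

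**Working it through.** **Order of events**

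1. Residents are part of the triad, and the triad is randomised once recruited (6.7).
2. Section 6.9.1 lists training of the intervention-group pharmacists after randomisation. Training given only to that group cannot be assigned before allocation is known.
3. Trained pharmacists deliver the intervention (6.4), so its start follows training and therefore randomisation.
4. Figure 1 puts baseline at that start, with a tolerance of a week on either side.
5. Section 6.9.2 treats the period after randomisation and around the start as one in which residents can still be swapped: "If a participant is excluded, as a post randomisation exclusion, they may be replaced, if this can be done within two weeks of the beginning" (meaning when delivery begins). A resident who joins this way can only be assessed after allocation.
6. No passage of the text shown places baseline assessment before randomisation.

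**The plan's own figure (section 6.8)**

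Inputs: rates of 1.50 and 1.178 per six months, 80% power, 5% two-sided (inferred from the 95% confidence interval), ICC 0.05, 44 clusters of mean 20, 20% loss.

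- Per arm, unclustered: (1.960 + 0.842)² × (1.50 + 1.178) / (1.50 − 1.178)² = 202.7.
- Design effect on the 16 residents per cluster left after loss: 1 + 15 × 0.05 = 1.75, giving 354.8 evaluable per arm.
- Divide by 0.8: 443.5 per arm, 887 in total, against 880 stated. Power at 440 per arm is 79.7%.

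The stated size reproduces. Re-timing baseline does not change it.

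**Effect of the window on baseline falls**

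Three months is about 13 weeks. A visit one week after the start puts 1/13 = 7.7% of the look-back inside delivery.

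Let f be the fraction of the look-back that is affected, s the share of the planned effect already present in that time, and b the log-log slope of follow-up falls on baseline falls. The protocol gives neither s nor b, so both are assumptions. The planned rate ratio is 1.178/1.50 = 0.785.

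- Baseline ratio between arms: r = 1 − f × s × (1 − 0.785).
- Adjusted rate ratio: 0.785 / r^b.

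| f | s | b | r | Adjusted ratio | Power |
|---|---|---|---|---|---|
| 0 | – | – | 1 | 0.785 | 79.7% |
| 1/13 | 0.25 | 0.3 | 0.996 | 0.786 | 79.3% |
| 1/13 | 1 | 1 | 0.983 | 0.799 | 74.2% |

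The last row needs the full effect from the first day of delivery and a slope of one. It is an upper bound on what the one-week tolerance can do through a real change in falls.

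**Rated measures and the Drug Burden Index**

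The protocol gives no figure from which to size these. The proxy EQ-5D-5L is rated at t1, so the whole rating falls after allocation. The Drug Burden Index is exposed only if the assessment falls in the week after the start.

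**Anchors**

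Falls and health-service use look back from baseline; hospitalisation looks back from randomisation. If follow-up runs from t1, hospital admissions between randomisation and t1 fall in neither period.

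**The case against.** The order is inferred from four sections rather than stated in one sentence, and the timeline, study flow chart and recruitment charts are not shown; they may give the sequence. That stands as a caveat. The inference is nevertheless tight, and the window in Figure 1 is explicit.

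The same one-week tolerance applies at all three visits, so it may be only a visit allowance. Falls come from care home records, so a late visit need not move the period covered. That also stands: 8% is maximum overlap, not bias.

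Four stronger readings are tempting, and the documents do not support them.

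- **The protocol contradicts itself on baseline.** Figure 1 says when hospitalisation data are collected; section 6.5 says what period they cover. Both can be true. The anchors are inconsistent across outcomes, which is a lesser fault.
- **A large part of the falls look-back is contaminated.** Gaps of 4 or 8 weeks between randomisation and start would put 4/13 = 31% or 8/13 = 62% of it after randomisation. The protocol states no such gap, and no service is delivered during it, so true falls have little reason to change. The worst case at 8 weeks (rate ratio 0.905, power 22%) requires the full effect in every week after randomisation, including before the service exists.
- **Proxy scores are biased by a known amount.** A baseline shift of 0.2 SD in one arm with a correlation of 0.5 would bias an adjusted difference by 0.5 × 0.2 = 0.1 SD, but both inputs are assumed. If the same shift persisted at six months, a clean baseline would leave 0.2 SD of bias and the shifted one 0.2 − 0.1 = 0.1 SD. The direction of harm is not determined.
- **Staff rate the Barthel, and baseline proxy scores are covariates.** Staff are named only for the EQ-5D-5L. Adjustment for baseline scores is inferred from the analogous model for secondary outcomes.

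Replaced residents cannot be assessed before allocation, so any fix must provide for them.

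**Conclusion.** The concern holds in limited form. Followed as written, the plan yields a baseline taken after allocation, up to a week into delivery, with no defined equivalent in control homes. This is a timing rule fixed in the protocol, so an analysis plan cannot repair it for the rated measures.

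The credible exposure is in two secondary outcomes: the staff-completed proxy EQ-5D-5L and the Drug Burden Index. Neither can be sized from the documents. For the primary outcome the window reaches at most about 8% of the look-back. Under the assumed ranges of s and b, the planned rate ratio of 0.785 would be estimated as 0.786 to 0.799, so bias is probably small. That conclusion covers the window only. Any further effect of the unstated interval before the start would have to come mainly through recording of falls. It also assumes that the figures not shown do not place baseline before randomisation.

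**What to change.** 1. State that proxy and self-reported EQ-5D-5L, Barthel and Drug Burden Index baselines are completed before allocation is disclosed to the home and practice.
2. End every record-based baseline look-back (falls, hospitalisation, resource use) at the randomisation date in both arms, so that Figure 1 and section 6.5 use one anchor.
3. Define t1 in control homes by the same calendar rule as in intervention homes.
4. For residents replaced after randomisation (sections 6.1.3.4 and 6.9.2), take record-based baselines to the same date and flag their proxy baselines as post-allocation.

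At the least, remove the plus-one-week allowance from t1. That ends exposure to delivery but not to knowledge of allocation.

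The cost is wording in the protocol and case report form, and possibly a slightly later release of allocation while forms are completed. Record-based items need only a different end date. Events between randomisation and t1 will lie outside the baseline window, and the protocol should say so. The sample size does not change.

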## 6.8 Sample Size

A sample size of 880 (440 in each arm) would detect a decrease in fall rate from 1.50 per individual over 6 months to 1.178 with 80% Statistical Power. This assumes that the number of clusters available will be 44, with a mean of 20 participants from each, a loss rate of no more than 20% and an ICC of 0.05 or less.

To balance any under recruitment with over recruitment (eventually balancing out over the whole study), we will recruit in all triads a mean of 20 participants. Any variation with these limits would need to be approved by TSG and or DMC.

These assumptions are based upon data from the CAREMED (29) study, which estimated a fall rate of 1.5 per individual over a 6 months period. The detectable difference (from 1.5 to 1.178) is a relative reduction of 21% which is half that detected within a UK based pharmacist led medication review service provided to care homes.

Data from the CAREMED (29) trial indicated a mortality rate of 33% and further loss to follow-up of 5% over 12 months. Thus, a reasonable estimate of total losses due to mortality or other reasons over 6-months would be 20%. However, we will use data, where possible, up to the point at which someone withdraws from the study (either voluntarily, or otherwise). Therefore, those lost to follow-up, for whatever reason, should contribute some information on falls rate to the study analysis.

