### 3. Resource use questionnaire (to be extracted from care home records)

- Participant study ID
- Patient status (nursing / residential, noting any change in the past 6 months)
- In the past three months has the care home been the participant's only place of residence?
  - Yes
  - No – details of time spent in the care home and time spent elsewhere (days/months)
- Has the patient had any falls in the past three month?
- In the past 6 months has the participant had any other health service contact?
  - No
  - Yes – details of numbers of visit(s) or consultations, and with whom

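### The protocol is inconsistent about the primary outcome's window: falls are sized over 6 months, but the 6-month falls item is labelled as the past 3 months

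*Protocol*

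**What the plan says.** Four places in the protocol bear on the window of the primary outcome.

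- **Section 6.8 (Sample Size)** uses a 6-month count: the planned sample "would detect a decrease in fall rate from 1.50 per individual over 6 months to 1.178 with 80% Statistical Power".
- **Section 6.5 (Primary Outcome)** reads "fall rate per person at 6 months; as documented in care home falls record". It names the source and the time point but not the look-back. The summary in Section 1.3 gives no window either.
- **Figure 1 (Section 6.6)** has one falls row, "Fall rate per person in past 3 months", marked at 0, 3 and 6 months.
- **Appendix 3, care home records questionnaire**, has one item on falls that have occurred: "Has the patient had any falls in the past three month". It asks for no number and no dates, and has no 6-month version.

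Three other statements matter. Section 6.5 has falls collected at 3 months as well as at 6 months. Section 6.10.4.1 plans a Poisson model of falls per patient. Section 6.5.1.3 refers the reader to Appendix 3 for the full list of data collected from participants.

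**The concern.** The window decides what the primary estimate is and how much information it carries, and the sections do not give the same window.

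A reader who follows the protocol's own usage can arrive at months 4 to 6. Section 1.3 lists a secondary fall rate at 3 months, Section 6.5 spells that out as falls in the preceding three months, and Figure 1 puts the same three-month label on the 6-month visit. Where the authors want a 6-month look-back they write one: health-service use at follow-up in Section 6.5, hospital stays and medications in Appendix 3, and the item directly after the falls question on the same form. Falls never get that option.

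Two things are at stake:

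- A researcher who extracts what Figure 1 and Appendix 3 describe may bring back only the last three months at the final visit. A 3-month extraction that was missed would then not be made good, although the care home record still holds those falls.
- Falls that were never extracted cannot be restored by a later analysis plan. This is why the point belongs in the protocol.

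**Working it through.** **Inputs.** From Section 6.8: 440 residents per arm, 44 clusters with a mean of 20, 20% loss, "an ICC of 0.05 or less" (taken as 0.05), and rates of 1.50 and 1.178 over 6 months. From Section 6.10.4.1: Poisson counts and a 5% level with a 95% confidence interval. Two-sided testing is assumed.

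**1. Reproduce the stated power.**
- Retained per arm: 440 × 0.8 = 352. Retained per cluster: 20 × 0.8 = 16.
- Design effect: 1 + (16 − 1) × 0.05 = 1.75.
- Effective number per arm: 352 / 1.75 = 201.1.
- Power = Φ(|λ1 − λ2| / √((λ1 + λ2)/n) − 1.96) = Φ(0.322 / √(2.678/201.1) − 1.96) = Φ(2.79 − 1.96) = **79.7%** (79.5% on the log scale).
- Required per arm for 80%: 443.5, against 440 stated.

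So the trial is sized on a 6-month count.

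**2. Both on-study windows counted and added.** With a constant fall rate, each 3-month window carries half: 0.75 against 0.589. Adding the two gives 1.50 against 1.178, so power is again **79.7%**.

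**3. Gaps between windows.** Figure 1 allows visits to move by a week either way, so fixed 3-month look-backs need not meet exactly. If a share c of the 26 weeks is covered (an assumption), both rates scale by c and the z value scales by √c.
- c = 25/26: **78.1%**.
- c = 24/26: **76.5%**.

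**4. Missed 3-month extractions.** The protocol gives no expected rate. As an illustration only, the pilot criterion in Section 6.5 accepts anything above 80% availability of 3-month falls data. If 20% of residents lacked the first half of their follow-up, c = 1 − 0.2 × 0.5 = 0.9 and power = Φ(2.79 × √0.9 − 1.96) = about 75%. This overlaps with the 20% loss already allowed for, to the extent that the missing residents died or left, so it leans pessimistic.

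**5. The 6-month item alone.** Months 4 to 6 with the same relative reduction: Φ(0.161 / √(1.339/201.1) − 1.96) = Φ(1.973 − 1.96) = **50.5%** (50.3% on the log scale). About 887 per arm would be needed for 80%. Sensitivity:
- Design effect at the full cluster size of 20 (1 + 19 × 0.05 = 1.95): 46.4%.
- ICC halved to 0.025, in case a shorter window clusters less: 60.5%.

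**The case against.** The strongest reply is that the 6-month window can be recovered from the text. Section 6.8 states it outright. Section 6.5 attaches a three-month look-back only to the secondary falls outcome at baseline and 3 months, and leaves it off the primary. Falls are collected at both 3 and 6 months, so the two windows run consecutively and together cover the intervention period. On that reading Figure 1 carries a loose row label and nothing is lost.

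Most of this stands, and it rules out three stronger readings that a reader might infer.

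- **That the trial has only about 50% power.** This needs the 6-month item to be analysed alone, which no section plans.
- **That the primary outcome is yes/no.** Under Poisson, any fall in three months has probability 1 − exp(−0.75) = 52.8% against 1 − exp(−0.589) = 44.5%, which gives 38.0% power with 201.1 per arm. But the planned model is for counts, the primary source is the care home falls record, and Appendix 3 describes the form holding the any-falls item as serving the economic evaluation. The case report form listed in Appendix 5 is not shown and may hold a count.
- **That residents who die or leave by month 3 drop out of the analysis.** Section 6.8 says data will be used where possible up to withdrawal, and Section 6.9.2 says data will be collected up to the end of participation.

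The reply does not remove the inconsistency. No section says that the windows are added, and the document contains no 6-month falls item. Summing also depends on the 3-month extraction having been done and on the visits falling so that no weeks are left out or counted twice.

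**Conclusion.** The point holds as an inconsistency about the window of the primary outcome, not as a demonstrated loss of power. The sample size counts falls over 6 months, the outcome definition gives no window, and the schedule and data list give three months.

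On the most natural reconciliation, adding the 3- and 6-month windows, power is 79.7% before losses from missed extractions or uncovered weeks. Those losses would be modest: 78.1% to 76.5% for one or two uncovered weeks. On the narrow reading of Figure 1 it would be about 50%, with a range of 46% to 60% over the design effects tried.

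These figures rest on Poisson variance, a constant fall rate, the same relative reduction in each half of follow-up, and two-sided testing at 5%.

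The matter should be settled in the protocol because it concerns the primary outcome and governs what is extracted at the final visit.

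**What to change.** - **Sections 1.3 and 6.5:** define the primary outcome as the number of falls in the care home falls record from day 0 (the 0-month point of Figure 1) to 6 months, or to the end of participation if earlier, relative to time at risk.
- **Figure 1 and Appendix 3:** make the 6-month item the number and dates of all falls since day 0. This recovers falls missed at a 3-month extraction or falling between visit windows, and dates prevent double counting.
- Keep the three-month look-back only for baseline and for the 3-month secondary outcome.

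Section 6.8 needs no change, since it already uses the 6-month count.

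The cost is wording in the protocol, with the case report form brought into line if it differs, and slightly more extraction time. The same record is opened at a visit that already takes place.
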